### Objectives

The primary objective is to evaluate the effectiveness of the DREAMT intervention (PreSAGE thermography-based AI monitoring with activity feedback dashboard) in increasing daily patient physical activity levels during inpatient rehabilitation, using a randomized multiple baseline design across participants.

The secondary objectives are to: (1) assess the impact on clinical rehabilitation outcomes, including Functional Independence Measure (FIM) scores, Functional Ambulation Category (FAC) scores, Modified Barthel Index (MBI), length of stay, discharge destination, and complications; (2) evaluate the effect on nursing workload distribution and time allocation; (3) explore the experiences, perceptions, and recommendations of patients, nursing staff, and therapists through semi-structured interviews; and (4) integrate quantitative and qualitative findings to develop a comprehensive understanding of intervention effectiveness and implementation considerations.

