### Outcome measures

The primary outcome is daily total active time (minutes per day), defined as time spent in non-lying postures (sitting on bed edge, sitting in chair, standing, walking, exercising) as continuously measured by the PreSAGE system. This outcome is aggregated daily and analysed as a within-patient time series. The validity of this AI-derived measure will be established against clinician-rated ground truth during Phase 2 validation (accuracy, precision, recall, F1, and AUROC), and only activity states meeting a pre-specified per-class reliability threshold (F1 ≥ 0.80) will contribute to the primary metric; states with lower reliability (for example, small-motion exercises) are reported descriptively and excluded from the primary outcome. Because individual rehabilitation prescriptions are heterogeneous and patient-specific, personalised therapist-set goals are evaluated as a patient-referenced secondary outcome rather than folded into the primary measure, which is defined identically for all participants to preserve comparability across the cohort.

Secondary quantitative outcomes include: (a) daily number and duration of sitting-out-of-bed episodes; (b) daily exercise frequency and duration, disaggregated by upper and lower limb exercises; (c) daily proportion of prescribed exercises completed (exercise compliance rate); (d) number of goals set and achieved per day; (e) dashboard utilization (daily interaction count and duration); (f) FIM score change from admission to discharge; (g) FAC score change; (h) MBI score change; (i) length of stay (days); (j) discharge destination (home, community hospital, skilled nursing facility); (k) incidence of complications (pressure injuries, deep vein thrombosis, falls, hospital-acquired infections); (l) nursing engagement frequency and duration across activity types (wound dressing, diaper change, dressing, intravenous management, patient calls, nasogastric tube feeding, assisted feeding, medication administration, vital signs monitoring), recorded as episode count and cumulative minutes per day; (m) time to first sit-out-of-bed episode post-admission; (n) complication rates (pressure injuries, deep vein thrombosis) analyzed by functional level subgroup.

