Secondary analyses for clinical outcomes (FIM, FAC, MBI, length of stay, discharge destination, complications) will use generalized linear models adjusted for baseline characteristics. Dashboard utilization patterns will be explored using descriptive statistics and latent class analysis to identify distinct engagement profiles. Subgroup analyses will compare intervention effects between functionally dependent and independent patients, with the hypothesis that dependent patients may show primary improvements in clinician-mediated outcomes (nursing engagement frequency, time to first sit-out, complication rates) while independent patients may show primary improvements in self-directed activity outcomes (daily active time, exercise compliance, dashboard utilization). The dose-response relationship between dashboard interaction frequency and activity changes will be examined using the interaction count as a time-varying covariate in the multilevel model.

All quantitative analyses will be conducted using R (R Foundation for Statistical Computing, Vienna, Austria) with the “lme4”, “nlme”, 'SingleCaseES', and “brms” packages.

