## Discussion

### Principal considerations

This protocol describes a rigorous mixed-methods approach to evaluating a novel thermography-based AI monitoring and feedback system in inpatient rehabilitation. The randomized multiple baseline design across participants represents a significant methodological advance over the pre-post and simple interrupted time series designs that predominate in digital health evaluations in rehabilitation settings.

The RMBD is well-suited to this study context for several reasons. First, the continuous within-patient time-series data generated by thermographic monitoring creates an unusually rich dataset that is best exploited by designs that model individual trajectories rather than group means at discrete timepoints. Second, the randomization of dashboard onset timing across participants provides a credible basis for causal inference: if activity increases systematically coincide with dashboard activation at five different randomly assigned timepoints, the effect is unlikely attributable to maturation, history, or regression to the mean (27, 28). Third, the design is ethical, as all patients receive the intervention during their admission; the only variation is the timing of onset. Fourth, the design does not require a separate no-treatment control group or multiple wards, making it feasible within a single-site context.

The piecewise multilevel growth model further strengthens the analysis by simultaneously modelling the natural recovery trajectory (pre-intervention slope), the immediate effect of dashboard activation (level change), and the sustained effect (post-intervention slope change), while accounting for between-patient heterogeneity and within-patient autocorrelation (42, 45). This provides more nuanced inference than a simple pre-post comparison.

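### Secondary objective 1 promises an impact on once-per-stay clinical outcomes, but the design has no treated-versus-untreated contrast for them

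*Protocol article*

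**What the plan says.** The Objectives section commits the trial to "assess the impact on clinical rehabilitation outcomes, including Functional Independence Measure (FIM) scores", together with FAC, MBI, length of stay, discharge destination and complications. Under Outcome measures, FIM is defined as "FIM score change from admission to discharge", with FAC and MBI change listed beside it. Length of stay and destination are single values per patient, and complications are an incidence not divided by phase. The same list contains "time to first sit-out-of-bed episode post-admission".

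For the clinical outcomes, the Quantitative analysis section says only that the analyses "will use generalized linear models adjusted for baseline characteristics". No exposure, comparator or phase term is given. The phase indicator in the piecewise multilevel model is specified for daily active time. Principal considerations states that "all patients receive the intervention during their admission; the only variation is the timing of onset" and that "the design does not require a separate no-treatment control group or multiple wards". A sentence closing the sensitivity analyses places all analyses under intention to treat by assigned onset day.

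**The concern.** The causal argument of the multiple baseline design rests on repeated daily measurements before and after a randomly timed switch. An outcome observed once per stay has no before and after. An admission-to-discharge change mixes baseline and dashboard days in every patient, and adjusting it for baseline characteristics describes prognosis unless some exposure is added. What remains for FIM, FAC and MBI is an uncontrolled pre-post change, not even divided at activation. The section on study rationale rejects pre-post designs for exactly this weakness, because maturation cannot be excluded.

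Time to first sit-out has a related problem. Its clock starts at admission, while activation comes on day 3 to 7, or later after weekend deferral. A first sit-out that precedes activation cannot respond to the dashboard, yet the subgroup hypothesis for dependent patients names this outcome.

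At stake is whether secondary objective 1 can be answered, and whether readers could take ordinary recovery for an intervention effect.

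**Working it through.** **Inputs from the protocol article.** Onset days 3, 4, 5, 6 and 7 with 10 patients each, N = 50 (Phase 3, Study design). Length of stay: median 24 days, SD 17.0, IQR 15–35 (Study setting; Sample size justification). The article gives no power statement for the clinical outcomes.

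**The plan's own figure.** Post-onset days at the median stay: 24 − 7 = 17 and 24 − 3 = 21. This matches the stated range of 17 to 21. No stated number is wrong; the problem is what can be identified.

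**Spread of exposure created by randomisation.** At 24 days the exposed share runs from 17/24 = 70.8% to 21/24 = 87.5%, a spread of 4/24 = 16.7 points. At 15 days it is 4/15 = 26.7 points; at 35 days, 4/35 = 11.4 points. No onset stratum is untreated.

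**Precision of the onset-day contrast.** Regress the outcome on assigned onset day:
- Sxx = 10 × (4 + 1 + 0 + 1 + 4) = 100
- SE of slope = SD/√100 = 0.1 SD per day
- Day-3 versus day-7 difference detectable with 80% power, two-sided 5%: 4 × 2.80 × 0.1 = 1.12 SD
- Length of stay: 4 × 2.80 × 17.0/10 ≈ 19 days, against a median of 24

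**What that means for a plausible effect.** Assume the effect accrues in proportion to days exposed, with d the effect in SD over a fully exposed stay of L days. The noncentrality is (d/L)/0.1, with 48 df. Both d and the proportionality are assumptions.

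| Stay L | Power, d = 0.5 | Power, d = 1.0 | d needed for 80% power |
|---|---|---|---|
| 15 days | 6.2% | 10.0% | 4.3 SD |
| 24 days | 5.5% | 6.9% | 6.9 SD |
| 35 days | 5.2% | 5.9% | 10.0 SD |

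The power is close to the 5% false-positive rate throughout.

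**Why mean change cannot stand in.** Suppose the dashboard has no effect and natural recovery equals 0.5 SD of the change score (assumed). A one-sample test with n = 50 has noncentrality 0.5 × √50 = 3.54 and is significant with probability about 93%. The article does not plan this test; the figure shows only that mean change is uninformative about the dashboard.

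**The case against.** The strongest reply is that one condensed sentence in an article is being read as a complete model. Adjustment for baseline implies some other term, and the intention-to-treat sentence is compatible with assigned onset day as that term; a fuller plan may say so. This stands as far as it goes. Leaving the exposure unnamed would be no finding by itself. But a fuller plan could only name onset day. It could not create an untreated comparator, and the word impact is already fixed in the objective.

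Several stronger readings are tempting and are not supported:
- A reader might infer that natural recovery will be reported as a dashboard effect. The article does not plan a test of mean change; this is a risk, not a stated intention.
- A reader might infer that most first sit-outs precede activation. The article gives no sit-out times.
- A reader might extend the point to every clinical outcome equally. Complications are datable events, and between days 3 and 7 the staggered onset does supply randomised patients not yet activated. The contrast exists in principle, over a short early window, but no phase split is planned.
- A reader might think the subgroup hypothesis is offered as confirmatory. The sample size section already labels functional-level subgroup comparisons exploratory. That label does not cover the clinical outcomes overall.

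It is also fair that low power for secondary outcomes is common, and that the 19-day figure uses the unadjusted SD of a skewed variable; covariate adjustment could reduce it. Finally, patients discharged before activation (the shortest Phase 1 stay was 4 days) are not usable controls, because they are selected by short stay.

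**Conclusion.** The point holds for FIM, FAC and MBI change, length of stay and discharge destination: as designed, the trial cannot separate a dashboard effect on them from natural recovery by any within-patient contrast. The one randomised contrast, earlier against later activation, has a detectable day-3 to day-7 difference of about 1.12 SD. That figure assumes 10 patients per onset day, a linear onset-day effect and no gain from covariates; the 5–10% power figures further assume effects of 0.5 to 1.0 SD accruing in proportion to exposure. For complications the gap is an unplanned phase split. For time to first sit-out it is that pre-activation events cannot respond, at an unknown frequency. The limitations section mentions none of this. The primary outcome is unaffected.

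**What to change.** - In secondary objective 1, replace the commitment to assess impact with one to describe these outcomes, and report them descriptively.
- If an effect estimate is wanted, specify assigned onset day (linear) as the exposure in the GLM, adjusted for the stratification factors (stroke versus non-stroke; FIM motor ≤58 versus >58). Report it with a 95% CI and label it exploratory.
- Report time to first sit-out descriptively, or analyse it from admission with activation, by assigned onset day, as a time-varying term, also exploratory. Do not restart the clock at activation among patients who have not yet sat out: that group is selected differently in each onset stratum, and all of its members are then treated.
- State in the limitations that the design's causal protection does not extend to once-per-stay outcomes.

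The cost is the wording of one objective, one model specification, a sentence in the limitations and a weaker claim on secondary outcomes. The article expects Phase 3 from the end of 2026, so the change can precede it.

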### Phase 3: randomized multiple baseline evaluation (months 13–24)

#### Study design

The primary quantitative evaluation employs a randomized multiple baseline design across participants (28, 29, 32), in which each patient undergoes two phases during their admission:
**Phase A (Baseline Observation):** From admission, the PreSAGE system continuously monitors patient activity. Activity data are collected and processed but no feedback is provided to the patient or treating team. This observation-only period provides individualized baseline data for each patient, lasting 3 to 7 days depending on the randomly assigned onset point (see Randomization below), consistent with the A phase in SCED methodology (27, 31).**Phase B (Dashboard Intervention):** At the randomly assigned onset point, the patient-facing dashboard is activated on a bedside tablet and the clinician-facing dashboard becomes available to the treating team. Therapists set personalized activity goals, and patients receive continuous feedback on their progress. Thermographic monitoring continues throughout.The critical design feature is the randomized timing of the A-to-B transition. Each patient will be randomly assigned, using a computer-generated allocation sequence with concealed envelopes, to one of five onset points: post-admission day 3, 4, 5, 6, or 7. If the assigned onset day falls on a weekend, activation will be deferred to the next weekday to ensure research assistant availability and clinical team presence for goal-setting. This ensures that each patient has a minimum baseline observation period of 72 h (to establish a stable pre-intervention trend) while staggering the transition point across the sample in a manner consistent with the MBD framework (29, 32). Ten patients will be assigned to each of the five onset strata, yielding 50 patients total.

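### Time to first sit-out runs from admission while both dashboards are off until day 3–7, so part of this outcome is settled before the intervention it is meant to reflect

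*Protocol article*

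**What the plan says.** Three parts of the protocol article bear on this.

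- **Outcome measures.** Secondary outcome (m) is "time to first sit-out-of-bed episode post-admission". The clock starts at admission.
- **Phase 3, Study design.** During the baseline phase, "Activity data are collected and processed but no feedback is provided to the patient or treating team". Only at onset is the patient tablet switched on, and only then "the clinician-facing dashboard becomes available to the treating team". Patients are randomized "to one of five onset points: post-admission day 3, 4, 5, 6, or 7", ten to each day. "If the assigned onset day falls on a weekend, activation will be deferred to the next weekday". On the length of the unexposed period: "This ensures that each patient has a minimum baseline observation period of 72 h".
- **Quantitative analysis.** The subgroup hypothesis is that "dependent patients may show primary improvements in clinician-mediated outcomes (nursing engagement frequency, time to first sit-out, complication rates"). Time to first sit-out is thus one of three outcomes named for dependent patients.

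Under The DREAMT intervention, the dashboard works mainly as a clinician tool for dependent patients. That route is closed until onset too.

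**The concern.** A first sit-out that happens before activation is fixed before the intervention can act. The article does not restart the clock at activation, limit the outcome to patients who have not yet sat out, or otherwise tie it to exposure.

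The outcome also sits badly with the design. Daily active time has values before and after onset in the same patient, which is what makes each patient their own control. A first sit-out occurs once and falls in one phase or the other, so that contrast does not exist for it. Every patient eventually receives the dashboard, so there is no never-exposed group either.

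At stake is one of the three outcomes through which the plan hopes to see benefit in dependent patients. If most first sit-outs come early, it will tend to show little difference even if the dashboard does promote sitting out.

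**Working it through.** The article states no figure for time to first sit-out, so there is none to reproduce. The check asks what share of first sit-outs would precede activation, under stated assumptions.

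**Inputs from the article.** Onset day d = 3, 4, 5, 6 or 7, in equal numbers; no feedback to anyone before onset; deferral from weekend to next weekday.

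**Assumption 1: exponential times with median m days.** Share before onset = 1 − 2^(−d/m), averaged over the five onset days. For m = 1, the terms 2^(−d) are 0.125, 0.0625, 0.0313, 0.0156 and 0.0078. Their mean is 0.048, so the share is 0.95.

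| Assumed median (days) | Share before assigned onset |
|---|---|
| 1 | 95% |
| 2 | 80% |
| 3 | 67% |
| 5 | 49% |
| 7 | 38% |

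**Assumption 2: constant daily probability p.** Share before onset = mean over d of 1 − (1 − p)^d. Deferral is added by assuming that admissions fall evenly over the week. This moves mean onset from day 5.0 to about 5.4. The latest onset is day 9: an assigned day 7 on a Saturday, deferred to Monday.

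| Assumed p | Assigned onset | With weekend deferral |
|---|---|---|
| 0.1 | 40% | 43% |
| 0.2 | 66% | 68% |
| 0.3 | 81% | 83% |
| 0.5 | 95% | 96% |
| 0.7 | 99% | 99% |

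More than half of first sit-outs precede the assigned onset once p exceeds about 0.13.

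**What the article hints about the likely range.** In the sample size section 18 min is 10% of daily active time, so the planning baseline is 18/0.10 = 180 min per day; 27/0.15 gives the same. The co-design decisions under Results count a sit-out episode from one minute. Both suggest early first sit-outs. But active time includes sitting on the bed edge, and 180 min is a whole-cohort planning value. Dependent patients (FIM motor score 58 or below) may sit out later.

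**How much signal is left between onset days.** Suppose activation doubles the daily probability to 2p. Mean time from admission is then [1 − (1 − p)^d]/p + (1 − p)^d/(2p). For p = 0.1 and d = 3 this is 0.271/0.1 + 0.729/0.2 = 6.4 days.

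| p | Mean, onset day 3 | Mean, onset day 7 |
|---|---|---|
| 0.1 | 6.4 days | 7.6 days |
| 0.3 | 2.8 days | 3.2 days |
| 0.5 | 1.9 days | 2.0 days |

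Even a doubling leaves a gap of 1.2 days between the extreme strata at p = 0.1 and about 0.1 day at p = 0.5, with ten patients per stratum before any split by functional level.

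**The case against.** Four arguments on the other side carry weight.

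1. **A randomized contrast exists.** Onset day is randomized, and the Quantitative analysis section analyses by assigned onset day. Comparing time from admission across onset days has a common time zero and is not biased. This stands. A reader might infer that the outcome cannot answer the question at all; the documents do not support that. The contrast is valid but diluted.
2. **The subgroup analysis compares intervention effects, not raw outcome levels.** A reader might infer that setting dependent against independent patients would merely measure disability. The text speaks of comparing effects between the groups, so that does not follow. What remains is that a once-only event offers no within-patient effect to compare.
3. **Nobody proposes to split first sit-outs by phase.** Such a split would carry immortal-time bias, since a post-onset first event requires no sit-out until onset. But the plan contains no such analysis, and counting from admission avoids the problem.
4. **The size is assumed.** At medians of 5 and 7 days, 51% and 62% of events follow assigned onset. Nor can early sit-outs be read off the therapy schedule: Study setting says therapy is given five days a week during the admission, without saying that it starts on day one or gets patients out of bed.

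It is also fair that the method for outcome (m) may be in an analysis plan not shown, so its absence here is no fault. But the time origin, the off-period and the hypothesis are all fixed in this article, and the mismatch lies between them.

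**Conclusion.** The point holds as a mismatch of timing. Outcome (m) starts at admission, the intervention starts on day 3 to 7 (up to day 9 with deferral), and the hypothesis for dependent patients still credits the intervention with improving (m). No first sit-out in the first 72 h can be affected in any stratum. The own-control logic does not reach this outcome, and the valid contrast between onset days is weakened by every event before onset.

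The share affected is unknown. The range of about 38% to 95% rests on assumed exponential times with medians of 7 days down to 1 day, and on assigned rather than deferred onset.

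Severity is minor. This is one of fourteen listed secondary outcomes, the hypothesis is worded as a possibility, and the sample size section declares functional-level subgroup comparisons exploratory. That section gives limited power as the reason, which is a different matter from events that precede exposure. The primary outcome and sample size are unaffected.

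**What to change.** In the dependent-patient hypothesis under Quantitative analysis, replace time to first sit-out with outcome (a), the daily number and duration of sitting-out episodes, analysed by phase in the multilevel model. It is already collected and has values on both sides of onset. It also keeps more information than a daily yes/no indicator, which could sit near its ceiling in both phases.

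Keep outcome (m) as a descriptive measure. It should not be labelled a baseline characteristic, because some events will follow activation. If it is kept as an effect outcome, analyse it from admission with activation as a time-dependent covariate, or by randomized onset day, and report how many patients had not yet sat out at onset.

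Before Phase 3 starts, use the Phase 1 recordings to find what share of patients, overall and with FIM motor score 58 or below, sit out before days 3 to 7. Phase 1 monitors from the bedside throughout the stay and extracts baseline FIM.

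The cost is a change of wording to one hypothesis and one secondary outcome, with no new data. The small downside is that one exploratory outcome loses its role as an effect measure.

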### The DREAMT intervention

The DREAMT intervention is a multi-component digital health intervention comprising:
(1)*Continuous thermographic monitoring:* The PreSAGE system provides automated 24-hour activity data capture, processing, and classification using validated AI algorithms.(2)*Patient-facing feedback dashboard:* For functionally independent patients, the dashboard is accessible via a bedside tablet, displaying daily activity summaries (active time, sitting episodes, exercise counts), graphical progress toward personalized goals, and motivational prompts. For functionally dependent patients who may be unable to independently access the tablet, the dashboard functions primarily as a clinician-facing tool, with the care team using activity data to guide nursing engagement, turning schedules, and early mobilization decisions.(3)*Therapist-guided goal setting:* At the point of dashboard activation, therapists set initial personalized activity goals (e.g., daily minutes of sitting out of bed, exercise repetitions) based on the patient's baseline data and clinical status. Goals are reviewed and adjusted every 2–3 days using dashboard data.(4)*Clinician-facing dashboard:* Providing the care team with activity trend data, nursing engagement metrics, sleep indicators, and patient progress visualizations to support clinical decision-making and care coordination.

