### Randomization and blinding

Randomization of dashboard onset timing will be performed using a computer-generated random number sequence, consistent with recommendations for randomized SCEDs (27, 28). Allocation will be concealed using sequentially numbered, opaque, sealed envelopes prepared by a statistician not involved in recruitment. Patients will be stratified by primary diagnosis (stroke vs. non-stroke) and baseline functional level [dependent [FIM motor score ≤58] vs. independent [FIM motor score >58]] to ensure balanced representation across onset strata. Neither patients nor clinical staff can be blinded to dashboard activation, as the intervention involves an active visual feedback display. However, the primary outcome (daily active time) is measured objectively and continuously by the PreSAGE system, eliminating observer bias in outcome ascertainment. The statistician conducting the primary analysis will be blinded to onset stratum assignments.

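### Dashboard utilization measures exposure to the intervention, so it should not be among the outcomes on which subgroup intervention effects are compared

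*Protocol article*

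**What the plan says.** The Quantitative analysis section states that "Subgroup analyses will compare intervention effects between functionally dependent and independent patients". It then gives a directional hypothesis for each subgroup. Dependent patients are expected to gain on three clinician-mediated outcomes: nursing engagement frequency, time to first sit-out and complication rates. For the others, "independent patients may show primary improvements in self-directed activity outcomes (daily active time, exercise compliance, dashboard utilization".

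Outcome measures lists the third item as secondary outcome (e): "dashboard utilization (daily interaction count and duration". It does not say whose interactions are counted.

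Four other statements bear on this:

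- Phase A, under Study design: "Activity data are collected and processed but no feedback is provided to the patient or treating team".
- Phase B, under Study design: only at onset is it the case that "the patient-facing dashboard is activated on a bedside tablet and the clinician-facing dashboard becomes available to the treating team".
- Delivery, under The DREAMT intervention: "For functionally independent patients, the dashboard is accessible via a bedside tablet", whereas "For functionally dependent patients who may be unable to independently access the tablet, the dashboard functions primarily as a clinician-facing tool".
- The subgroup split, under Randomization and blinding: "baseline functional level [dependent [FIM motor score ≤58] vs. independent [FIM motor score >58".

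The Quantitative analysis section also plans descriptive statistics and latent class analysis of utilization, and enters the daily interaction count in the multilevel model as a covariate to study dose-response. The Sample size justification calls the functional-level subgroup comparisons exploratory and hypothesis-generating.

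**The concern.** The design draws its causal force from comparing each patient's days before onset with the days after it, at randomly staggered onset times. An outcome fits that logic only if it could take different values before onset and could stay unchanged after it. Utilization meets neither condition. Before onset there is no dashboard to use. After onset, any use is a rise from zero, whether or not the patient moves more.

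The subgroup contrast has a second problem. Functional level decides in part who is handed a usable tablet, so a gap in patients' tablet use between subgroups is partly a record of delivery.

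At stake is the reading of the exploratory result. A rise in utilization among independent patients, or a gap in their favour, could be reported as support for the idea that they respond through self-directed behaviour, although activity does not enter the measure.

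**Working it through.** The protocol gives no power, error rate or expected value for utilization or for this subgroup comparison, so there is no figure to reproduce. The argument is structural.

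**Step 1: the within-patient contrast.** Take the protocol's level-1 model with utilization as Y:

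Y = β0 + β1·Day + β2·Phase + β3·Day_post + e.

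In Phase A, Y = 0 on every day for every patient, so β0 + β1·Day = 0 throughout baseline and there is no baseline variation. In Phase B, what remains is β2 + β3·Day_post, which is simply the mean use on that day. The nominal effect is therefore

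(mean use in B) − (mean use in A) = (mean use in B) − 0 = mean use in B.

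Randomized onset does not rescue it. On a given day after admission, patients still in Phase A have zero use because they have no dashboard, so they say nothing about what use would otherwise have been.

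**Step 2: the subgroup contrast.** The difference in nominal effects is

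(B use, independent − 0) − (B use, dependent − 0) = B use, independent − B use, dependent.

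This is a difference in how much the dashboard was used. If only patients' tablet interactions count, The DREAMT intervention section already gives a reason for it: the tablet is the route for independent patients, and the dashboard is mainly a clinician tool for dependent patients who may be unable to reach it.

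**Step 3: the two roles side by side.**

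| Where in Quantitative analysis | Role of utilization |
|---|---|
| Subgroup hypothesis | Response: an outcome expected to improve |
| Dose-response analysis | Exposure: a covariate explaining change in activity |

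The same variable cannot be both the dose and the evidence that the dose worked.

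**Step 4: illustration only.** Usage rates and subgroup sizes are not in the protocol, so the following are assumptions: 50 patients, 10 per onset day 3 to 7, 24 days each; splits of 25/25, 35/15 and 15/35 (independent/dependent); Poisson use with gamma variation between patients (shape 1); no effect on activity; 2,000 simulated trials per setting; tests at two-sided 0.05.

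- Change from A to B in independent patients (one-sample t-test): significant in 99.7% to 100% of trials.
- Independent significantly above dependent (Welch test), by assumed use per day:

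| Independent vs dependent | Ratio | Share of trials |
|---|---|---|
| 1 vs 0.5 | 2:1 | 36% to 61% |
| 3 vs 1 | 3:1 | 75% to 96% |
| 2 vs 0.5 | 4:1 | 90% to 99% |
| 3 vs 0.2 | 15:1 | above 99% |
| 2 vs 2 | 1:1 | 1% to 5% |

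- A null activity outcome compared between subgroups: about 5%, as it should be.

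The unequal rows show power to detect a real difference in use that was assumed. They are not type I error rates, and the conclusion does not depend on them.

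**The case against.** The strongest case against the point is that it is one item in a parenthesis. The hypothesis names six outcomes, three per subgroup, says only what patients may show, and has no decision rule. The subgroup comparisons are declared exploratory. The protocol already plans to describe utilization and to use it as a dose, so much of the proper handling is in place. All of this stands, and it limits the point to one limb of an exploratory hypothesis.

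Three stronger readings are tempting and are not supported:

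- *That the subgroup hypothesis is confirmed whatever the dashboard does.* Daily active time and exercise compliance are not positive by construction, nor are the outcomes named for dependent patients, and nothing lets utilization decide alone.
- *That use must be lower in dependent patients.* The text says only that they may be unable to reach the tablet and that the dashboard is primarily clinician-facing. If clinician interactions count, the direction is open.
- *That a false difference will be carried into the integrated conclusions.* The Mixed-Methods integration section asks for whom activity improves, and its example keeps interaction rates and activity gains apart. Misreading is possible there but is not planned.

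None of these objections reaches the zero baseline or the double role as dose and response. Both hold for any usage rate and whichever interactions are counted.

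**Conclusion.** The point holds in limited form. No intervention effect on dashboard utilization can be estimated in this design, and a subgroup difference in patients' tablet use would reflect delivery mode rather than a different response. One of the three outcomes named for independent patients is therefore uninformative as evidence of effect or of effect modification.

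The first part rests only on the protocol's own statement that both dashboard views start at onset. The second assumes that utilization means patients' own tablet use, which the protocol leaves unstated. The primary outcome, its power and the other five outcomes in the subgroup hypothesis are unaffected, and no confirmatory claim is at risk.

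**What to change.** 1. In Quantitative analysis, delete dashboard utilization from the outcomes on which independent patients are expected to improve.
2. In Outcome measures, classify item (e) as an engagement or exposure measure, reported descriptively for Phase B by functional level, and state whether patient interactions, clinician interactions or both (separately) are counted.
3. Rest the self-directed hypothesis on the phase-by-functional-level contrast for daily active time and exercise compliance. Exercise compliance stays, since nothing here counts against it.

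The planned latent class and dose-response analyses can remain. The cost is wording: no data collection changes, utilization is still reported, and the only thing removed is a comparison that could not inform. Phase 3 is expected to start at the end of 2026, so the text can be changed before any evaluation data exist.
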